#### Body Mass Index (BMI)

To calculate BMI, participants will be asked to report their height in centimetres and their weight in kilograms. Conversion tables will accompany these questions so that participants can convert their height from feet and inches into centimetres and their weight from stone into kilograms if needed.

#### Sociodemographic characteristics

Sociodemographic characteristics such as age, sex, country of birth, Aboriginal or Torres Strait Islander origin, marital status, employment status and highest level of education will be recorded at baseline.

### Process measures

During the baseline survey, the computer software will record the number of intervention group participants who elect to be sent the hyperlink for each online program and referred to each telephone service. As part of the 6-month follow-up survey the number of intervention group participants who report using each online program and/or telephone service in the past 6 months and exposure to these interventions will be determined.

### Statistical analysis

Descriptive statistics will be used to present baseline characteristics for the intervention and control groups. Logistic regression will be used to test if there is a statistically significant difference in the change in prevalence of daily smoking between the two treatment groups. The outcome in the model will be smoking status and the predictors will include time, group and an interaction term between time and group. The *p*-value associated with the interaction term will be used to determine if there was a statistically significant difference in change between the groups. Linear regression will be used to test if there was a statistically significant different change in the mean level of the other outcomes between the groups. The outcome in each model will be the participant’s value of the outcome measure post treatment and the predictors will include their baseline value and treatment group (i.e., Analysis of Covariance). The p-value associated with treatment group will be used to determine if there was a statistically significant difference in the change from baseline to follow-up between the groups. Both the logistic and linear regression models will also be fit within a Generalised Estimating Equation framework to adjust for the correlation of responses within classes. All analyses will be conducted according to the Intention To Treat principle and the approach suggested by White and colleagues will be used to handle missing data [47]. The initial analysis will include all available data and will be valid under the assumption that the missing data are missing completely at random. Sensitivity analyses will be conducted under different assumptions about the missing data mechanism.

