### Randomisation

The randomisation sequence will be generated by an independent statistician using a random number function in Microsoft Excel. An equal number of classes will be randomised to each condition (1:1) using a randomised block design, with a block size of six, to ensure the conditions are balanced. Participant blinding will not be possible because they will be aware of the trial’s conditions and the differences will be apparent.

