### Recruitment and baseline survey

An information letter describing the trial and intervention and control conditions will be distributed to students. A week later, students will be provided with a verbal explanation of the study in class and invited to complete the baseline survey using a computer tablet. Informed consent will be recorded via the first page of the online baseline survey which will explain that if the student would like to take part in the trial they should choose ‘Next’ and if they do so they agree to participate in the trial. Across the 100 classes, approximately 1,100 eligible TAFE students will be approached, and assuming the 92 % response fraction achieved in pilot work, we expect 1,012 students to be recruited into the trial and complete the baseline survey. The baseline survey will include standard and validated questions to examine the student’s current smoking, alcohol consumption, daily fruit and vegetable intake, and physical activity. Students’ knowledge of the Australian guidelines for each risk behaviour and intentions to change behaviours that do not meet Australian guidelines will be assessed. Socio-demographic characteristics, self-reported height, self-reported weight, and type of TAFE course students are studying will also be collected at baseline.

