### Sample size

As there are five primary endpoints (smoking, alcohol consumption, fruit intake, vegetable intake and physical activity) an alpha level of 0.01 will be used to adjust for the multiple comparisons. The prevalence of daily smoking in the control group at follow-up is expected to be 22 % [11]. We aim to recruit 1012 TAFE students at baseline (i.e., 506 per condition). Allowing for 20 % loss to follow-up at 6 months, data will be available for 405 participants per condition. With an expected intra-cluster correlation coefficient (ICC) of 0.005 this will give the study a design effect of approximately 1.04 and an effective sample size of 389 per group, which will provide 80 % power to find an absolute difference of 9.5 % (in daily smoking rates) between the groups at the follow-up visit. Allowing for a higher ICC for the continuous outcomes (0.01), the study will have 80 % power to detect an absolute difference of 0.25 SD in these measures at the 1 % significance level, which equates to a difference of approximately 1.25 standard drinks of alcohol, 0.25 pieces of fruit, 0.25 vegetables and 50 MET minutes of physical activity per week.

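### Allocation is not stratified by course type, and the four continuous-outcome models leave out course type, sex and age although all are collected: a small, avoidable loss of balance and precision

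*Protocol article*

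**What the plan says.** **Allocation.** Under Randomisation: "An equal number of classes will be randomised to each condition", in a 1:1 ratio with a block size of six. The stated purpose is balance between conditions. No stratification factor is named. The Design section fixes 100 classes, 50 per condition.

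**Models.** Under Statistical analysis, the four continuous outcomes (alcohol, fruit, vegetables, physical activity) are analysed by ANCOVA, where "the predictors will include their baseline value and treatment group". Daily smoking is analysed by logistic regression on time, group and their interaction, and the interaction is the test. Both model types are fitted by GEE to allow for correlation within classes.

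**Data in hand.** Under Recruitment and baseline survey: "type of TAFE course students are studying will also be collected at baseline". Age and sex are listed under Sociodemographic characteristics.

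**Planning values.** The Sample size section gives, for smoking, an "expected intra-cluster correlation coefficient (ICC) of 0.005", and 0.01 for the continuous outcomes. It adds that "an alpha level of 0.01 will be used to adjust for the multiple comparisons", and claims "80 % power to detect an absolute difference of 0.25 SD in these measures at the 1 % significance level".

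**The concern.** The randomised unit is a class within one course. The Background lists courses as unlike as hairdressing, plumbing, automotive trades and commercial cookery. It is plausible that course type, with the age and sex mix that goes with it, accounts for part of the difference between classes in drinking, diet and activity. The article gives no outcome data by course, so this is an inference.

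If it is so, two things follow. Blocking on the count of classes leaves course mix to chance. And the part of the course effect that the baseline value does not absorb stays in the residual variance of the treatment comparison. At stake are precision and face-validity balance. Validity is not at stake, because an unadjusted comparison is sound under class randomisation.

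**Working it through.** **1. The plan's own figures.** Analysed class size is 810/100 = 8.1.
- Smoking: design effect 1 + 7.1 × 0.005 = 1.0355, which rounds to 1.04; 405/1.04 = 389. The continuity-corrected formula for 22% against 12.5% (two-sided alpha 0.01, 80% power) also gives 389 per arm.
- Continuous: design effect 1 + 7.1 × 0.01 = 1.071; effective n = 405/1.071 = 378. The detectable difference is (2.576 + 0.842) × √(2/378) = 0.2485 SD.

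Both claims reproduce. Two-sided testing is assumed because it returns the stated numbers. The calculation takes no credit for any covariate, not even the baseline value.

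**2. Chance imbalance in course mix.** Assume 50 of the 100 classes are of one type and that class order is unrelated to type. The number X of that type in one arm is then hypergeometric (100, 50, 50), and the arm difference is (2X − 50)/50.
- SD of the difference: 10 points.
- P(difference ≥ 10 points) = 32%. Differences move in steps of 4 points, so this means 12 or more.
- P(difference ≥ 20 points) = 7%.

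**3. Power gain from the covariates, starting from the planned model.** Let r be the baseline–follow-up correlation and R² the share of remaining variance that course type, sex and age explain. The article gives neither, so both are assumptions. Residual SD is s = √((1 − r²)(1 − R²)), and power at 0.25 SD is Φ(0.25/(s√(2/378)) − 2.576).

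| r | R² = 0 | R² = 1% | R² = 5% | R² = 10% |
|---|---|---|---|---|
| 0.5 | 91.8% | 92.1% | 93.3% | 94.6% |
| 0.6 | 95.7% | 95.9% | 96.7% | 97.5% |

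At R² = 5% the gain is 1.5 points (r = 0.5) or 1.0 point (r = 0.6). The detectable difference shrinks by 0.5% to 5.1% as R² runs from 1% to 10%.

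**4. Course type alone.** Two equal course groups g SD apart contribute between-class variance (g/2)², that is an ICC of about 0.01, 0.04 and 0.09 for g = 0.2, 0.4 and 0.6. Take 100 classes of 8, r = 0.6, and an ICC of 0.01 within course type.
- Residual variance of a class mean after baseline adjustment: 0.64 × (0.01 + 0.99/8) = 0.0856.
- Pooled baseline slope: b = (0.6 + g²/4)/(1 + g²/4).
- Course variance left over: ((1 − b)g)²/4.
- Cost of estimating the course term: a factor 1/(1 − 1/99) = 1.010.

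| g | b | left over | variance ratio with/without course type |
|---|---|---|---|
| 0.2 | 0.604 | 0.0016 | 0.0865/0.0872 = 0.99 |
| 0.4 | 0.615 | 0.0059 | 0.0865/0.0915 = 0.95 |
| 0.6 | 0.633 | 0.0121 | 0.0865/0.0977 = 0.88 |

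Simulations of the same setting give 0.99 to 1.00, 0.95 to 0.96 and 0.87 to 0.90. The 0.2 SD gap is the only one of the three compatible with the planning ICC of 0.01, and there the gain is near zero.

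**5. If the ICC is higher than planned.** With r = 0.5 and no further covariates, effective n is 405/1.142 = 355 at an assumed ICC of 0.02 and 405/1.355 = 299 at 0.05. Power at 0.25 SD is then 89.8% and 83.0%, against 91.8% at 0.01. This is where course group would have something to recover.

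**The case against.** The strongest reply is that this is an efficiency preference. The model description says what predictors will be included and does not close the list, and an article commonly leaves further covariates to the analysis plan. Chance imbalance is already reflected in the standard error. The planned baseline adjustment does most of the work: at an assumed r = 0.5 it cuts the detectable difference by 13%, from 0.2485 to 0.2152 SD, against 0.5% to 5% for the omitted covariates.

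Most of this stands, and it limits the point to an optional improvement. It has less force for allocation. The article does state the ratio, block size and balancing aim, and an analysis plan cannot add stratification once classes are allocated.

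A reader might extend the point to the smoking model. The documents do not support that. The test there is a time-by-group interaction, and the group term already absorbs baseline differences between arms. Course type, sex and age are taken at baseline and do not vary over the model's time term, so entering them as main effects need not sharpen the interaction. Adjustment in a logistic model also changes the odds ratio being estimated.

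**Conclusion.** The point holds as a modest one about balance and precision, for the allocation and the four continuous outcomes only. A substantial course-mix imbalance is quite possible (about 32% for 10 or more points and 7% for 20 or more, if half the classes are of one type). Prespecified covariates would add about 1 to 1.5 points of power at 0.25 SD, assuming r of 0.5 to 0.6 and 5% of residual variance explained. Course type alone adds almost nothing at ICC 0.01. It would cut the variance by about 5% and 12% for gaps of 0.4 and 0.6 SD, which imply ICCs of 0.04 and 0.09, well above the planning value.

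A reader might infer that the trial is underpowered or its estimates biased. Neither follows: the stated power reproduces without these covariates, and randomisation protects the comparison. Nor would adjustment abolish imbalance or between-class variance; it would reduce their effect, at a small cost.

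**What to change.** Name broad course group (two or three categories), sex and age in advance as covariates in the four continuous-outcome GEE/ANCOVA models, alongside baseline value and group. If allocation has not yet been done, randomise classes within those course groups and keep the stratum in the same models. Leave the smoking model as it is on this account.

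Cost: no new data, and a sentence in each of the two sections. The downsides are a few degrees of freedom, the need to define course groups before allocation (the article gives no course counts to show how many are workable), and possibly incomplete blocks in a small group.

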### Follow-up survey

The follow-up survey will be administered via computer tablet to the same students while in class, 6 months after recruitment. Based on TAFE records of student retention in courses, it is expected that the trial’s retention rate will be about 80 %, which will result in approximately 810 students (405 per condition) completing the 6-month assessment. The students’ sex, year of birth, TAFE class, and first and last letters of mother’s first name will be used to link baseline and follow-up survey data. The probability of a mismatch using this procedure has been calculated to be <1 in 148 000 [40]. The 6-month assessment will examine TAFE students’ current smoking, alcohol consumption, fruit and vegetable intakes and physical activity, knowledge of Australian health guidelines and intentions regarding changing health risk behaviours.

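### The main analysis is rested on data missing completely at random; the smoking model is the exposed endpoint, because it does not condition on each student's baseline smoking

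*Protocol article*

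**What the plan says.** All references are to the protocol article.

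- **Statistical analysis, missing data.** The stated principle is "All analyses will be conducted according to the Intention To Treat principle", with a missing-data approach taken from a cited paper that the article does not describe. Then: "The initial analysis will include all available data and will be valid under the assumption that the missing data are missing completely at random". The rest is covered by "Sensitivity analyses will be conducted under different assumptions about the missing data mechanism".
- **Statistical analysis, smoking.** The outcome is smoking status and "the predictors will include time, group and an interaction term between time and group". The interaction p-value decides.
- **Statistical analysis, other four outcomes.** The six-month value is the outcome and "the predictors will include their baseline value and treatment group". Both kinds of model are fitted by GEE to allow for correlation within classes.
- **Follow-up survey.** The 80% retention figure is introduced with "Based on TAFE records of student retention in courses, it is expected that", and the survey is done on tablets in class.
- **Sample size.** "Allowing for 20 % loss to follow-up at 6 months, data will be available for 405 participants per condition".
- **Recruitment and baseline survey; Sociodemographic characteristics.** The five behaviours, course type, age, sex, employment, education and other characteristics are collected at baseline.

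**The concern.** Missing completely at random means that leaving the study is unrelated to anything about the student, measured or not. Here a student who has left the course is not reached by an in-class survey. The article does not argue that leaving a course is unrelated to smoking, drinking, age or education. A link is an inference, but the stated assumption allows none.

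The smoking model makes this matter. Every recruited student contributes to baseline prevalence and only those still in class contribute to follow-up prevalence. The model has no term for the individual's own baseline smoking. If smokers leave one arm disproportionately, that arm's prevalence appears to fall without anyone having quit, and the time-by-group term picks this up as an intervention effect. The trial is unblinded, and only the intervention arm gets feedback, referral and reminders, so a difference in loss between arms cannot be excluded. At stake is whether the 1% test for smoking keeps its error rate.

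**Working it through.** **1. The plan's own figures.** 506 × 0.80 = 404.8, so 405 per arm. Class size at follow-up is 405/50 = 8.1, so the design effect is 1 + (8.1 − 1) × 0.005 = 1.036, and 405/1.04 = 389. For 22% against 12.5% at two-sided 1% and 80% power, the continuity-corrected requirement is also 389 per group. The loss and sample-size figures are consistent, and this point changes neither.

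**2. Inputs for the smoking check.**

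- From the article: 22% daily smoking (given for controls at follow-up; assumed here at both times in both arms, so no effect), 506 per arm at baseline, about 20% loss, alpha 0.01.
- Assumed: the reference arm loses 20% of smokers and non-smokers alike. The selective arm loses fraction *a* of baseline smokers and *b* of baseline non-smokers, either 30%/17% or 35%/16%.
- Assumed: tracking difference *d* = P(smokes at 6 months | baseline smoker) − P(smokes at 6 months | baseline non-smoker), 0.6 or 0.8.
- Two-sided testing is assumed.

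**3. Formulas.**

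- Smokers' share among those retained: q = 0.22(1 − a) / [0.22(1 − a) + 0.78(1 − b)]. For 30%/17%: 0.154/(0.154 + 0.6474) = 0.192. For 35%/16%: 0.143/(0.143 + 0.6552) = 0.179.
- Observed follow-up prevalence in that arm: f = 0.22 − d(0.22 − q).
- Interaction odds ratio under no effect: [f/(1 − f)] / [0.22/0.78].
- Variance, reference arm: (1/506 + 1/405 − 2d/506)/0.1716, where 0.1716 = 0.22 × 0.78.
- Variance, selective arm: 1/(506 × 0.1716) + 1/(n₁f(1 − f)) − 2c/(506 × 0.1716 × f(1 − f)), with n₁ the number retained and c = q(0.22 + 0.78d − f).
- Rate: Φ(−2.576 + |ln OR|/SE) + Φ(−2.576 − |ln OR|/SE).

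Example, 35%/16% with d = 0.8: f = 0.22 − 0.8 × 0.0408 = 0.1873. OR = 0.2305/0.2821 = 0.817, so ln OR = −0.202. n₁ = 506 × 0.7982 = 403.9 and c = 0.1792 × (0.844 − 0.1873) = 0.1176. The selective-arm variance is 0.01152 + 0.01626 − 0.01780 = 0.00998 and the reference-arm variance is 0.00748. SE = √0.01746 = 0.132, 0.202/0.132 = 1.53, and the rate is Φ(−1.05) = 14.7%.

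| Loss in one arm (smokers / non-smokers) | Overall loss | d | f | OR under no effect | SE | False-positive rate |
|---|---|---|---|---|---|---|
| 20% / 20% | 20.0% | either | 0.220 | 1.00 | – | 1.0% |
| 30% / 17% | 19.9% | 0.6 | 0.203 | 0.905 | 0.160 | 2.6% |
| 30% / 17% | 19.9% | 0.8 | 0.198 | 0.874 | 0.128 | 6.4% |
| 35% / 16% | 20.2% | 0.6 | 0.195 | 0.861 | 0.163 | 4.9% |
| 35% / 16% | 20.2% | 0.8 | 0.187 | 0.817 | 0.132 | 14.7% |

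These formulas ignore clustering. Simulations with class-robust standard errors gave odds ratios of 0.82 to 0.91, rejection of about 3% for 30%/17% at d = 0.6, about 6% for 30%/17% at d = 0.8, and 14% to 16% for 35%/16% at d = 0.8.

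**4. Two contrasts.** If the same selective loss occurs in both arms, f is equal in both and the interaction is null; simulation kept about 1%. If 6-month smoking is instead modelled on group and baseline smoking among those followed, rejection returns to about 1% with an odds ratio of about 1.00 in the one-arm scenarios.

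**5. The other four outcomes.** A large simulation under no effect used 20% loss and follow-up = 0.6 × baseline + 0.3 × another baseline predictor + noise. Completers' ANCOVA was biased by less than 0.005 SD when loss depended on the outcome's own baseline value in one arm. The bias was about 0.05 SD when loss in one arm depended on the omitted predictor; adding that predictor removed it. It was about 0.10 SD when loss depended on the follow-up value itself. The detectable effect is 0.25 SD.

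**The case against.** Four objections carry weight.

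- **The text does not say only.** It says that the initial analysis is valid under this assumption. A reader might infer that all five primary analyses fail without it. That does not follow: for four outcomes the model conditions on baseline value and arm and tolerates loss that depends on those, so the sentence is stricter than these models need. This stands, and narrows the point mainly to smoking.
- **Outcome-related drop-out is not enough.** A reader might infer that smokers leaving courses more often already biases the comparison. Under no effect it does not; the loss must also differ by arm. The documents give no figures showing that it will, and the follow-up procedure is the same in both arms. This stands, so the size of the bias is conditional.
- **Comparing follow-up prevalences is not the planned test.** One might set 19.2% against 22%, a 2.8-point gap. That assumes nobody changes smoking status and ignores the baseline term. The table therefore uses the interaction test and incomplete tracking.
- **Sensitivity analyses and a cited approach are planned.** Their detail is commonly left to the analysis plan, so its absence from the article is no fault. They do not alter the assumption declared for the main result.

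Calling the initial analysis the main one is a reading. It is a fair one, since every alternative is labelled a sensitivity analysis.

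**Conclusion.** The point holds in limited form. The article commits its main analysis to an assumption that is hard to defend for loss through course drop-out, while holding the baseline data that would allow a weaker one.

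The practical exposure is the smoking interaction test. It is biased if loss depends on baseline smoking and differs by arm. Under the assumed one-arm patterns and tracking of 0.6 to 0.8, the odds ratio under no effect is about 0.82 to 0.90 and the false-positive rate about 3% to 15% instead of 1%. With unselective loss, or the same pattern in both arms, there is no bias under no effect. The loss splits and tracking values are assumptions, not figures from the documents.

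For the four continuous outcomes the remaining exposure is small: about 0.05 SD if an unadjusted baseline predictor drives loss in one arm. This is a worthwhile, cheap improvement, not evidence that the primary results would be invalid.

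**What to change.** Make the main analysis valid under missing at random, given arm and recorded baseline data.

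- **Smoking:** model 6-month daily smoking on group and baseline smoking in the class-level GEE, matching the approach already planned for the other outcomes.
- **All five outcomes:** bring in baseline predictors of drop-out (age, sex, education, employment, course type), as covariates, through weighting, or by multiple imputation within arm that allows for class. Multiple imputation is one acceptable route, not a requirement.
- **Wording:** replace the missing-completely-at-random sentence accordingly, and keep the unadjusted available-data analysis as a sensitivity analysis.

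The planned sensitivity analyses are still needed, because none of this covers loss that depends on the unobserved 6-month value itself.

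**Cost:** modest extra programming, no new data and no change in sample size. Linking baseline to follow-up records is already required for the other four outcomes. The smoking odds ratio from the covariate-adjusted model becomes conditional on baseline smoking instead of marginal, which should be stated when it is reported.
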